### Outcome measures

An overview of all outcome measures and assessment points is presented in Table 2. Additional details of the measures, including psychometric properties and time of application, are provided in the full study protocol available in Supplementary File 1. All clinician-rated measures will be collected face-to-face (or via videoconference or telephone, when face-to-face assessments are not feasible). All self- and parent-reported measures are administered via an online platform (BASS), which ensures automatic and complete entry of each measure into the trial database.

**Table 2 Tab2:**
[figure not shown]
Overview of measures

Abbreviations: *AAI* Appearance Anxiety Index, *BDD-YBOCS-A* Yale-Brown Obsessive-Compulsive Scale Modified for Body Dysmorphic Disorder, Adolescent version, *CGAS *Children’s Global Assessment Scale, *CGI-I* Clinical Global Impressions Scale—Improvement, *CGI-S* Clinical Global Impressions Scale—Severity, *CHU9D* Child Health Utility 9D, *CRAFFT* acronym for the key words Car, Relax, Alone, Forget, Friends and Trouble, *CSQ-8* Client Satisfaction Questionnaire, *DIAMOND-KID* Diagnostic Interview for Anxiety, Mood, and OCD and Related Neuropsychiatric Disorders—Child and adolescent version, *DSHI* Deliberate Self-Harm Inventory Youth version, *GAD-7* Generalized Anxiety Disorder—7-item scale, *OCD-RD interview* obsessive-compulsive disorder and related disorders interview, *PEAS* Patient Exposure Adherence Scale, *PRAS* Patient Relaxation Adherence Scale, *SMFQ* Short Mood and Feeling Questionnaire, *TCES* Treatment Credibility and Expectancy Scale, *TiC-P* Treatment Inventory of Costs in Patients with Psychiatric Disorders, *WAI-C/P* Working Alliance Inventory—child and parent version, *WSAS-Y/P* Work and Social Adjustment Scale—youth and parent version

#### Baseline measures

Psychiatric diagnoses will be based on DSM-5 diagnostic criteria. A semi-structured interview based on DSM-5 criteria, the Diagnostic Interview for Anxiety, Mood, and OCD and Related Neuropsychiatric Disorders – Child and Adolescent Version (DIAMOND-KID) [36], will be used. Additional obsesive-compulsive related comorbidities not included in the DIAMOND-KID (e.g., olfactory reference syndrome) will be assessed using separate modeules from the Structured Clinical Interview for DSM-IV (SCID-I) [37].

#### Primary outcome measure

The primary outcome measure is the clinician-rated BDD-YBOCS-A [38, 39], measured at post-treatment and 1 (primary endpoint), 3, and 6 months after treatment completion. The BDD-YBOCS-A contains 12 items ranging from 0 to 4, including five questions on obsessions, five on compulsions, one about insight, and one to measure behavioral avoidance. The total BDD severity score ranges from 0 to 48, with higher scores denoting higher severity. The BDD-YBOCS-A has good psychometric properties [39] and is the gold standard in the BDD field to assess symptom severity. All assessors performing baseline evaluations and blinded assessors are extensively trained on the BDD-YBOCS-A by clinical experts at each site. Outcome assessors are trained to reliability (see the full study protocol in Supplementary File 1 for a complete description of the training procedures and establishing of the inter-rater reliability).

#### Secondary outcome measures

Treatment response and full or partial remission rates will be calculated at each follow-up point. Following current consensus in the field [40], treatment response will be defined as a reduction ≥30% on the BDD-YBOCS-A from baseline and full or partial remission will be defined as a total score ≤16 on the BDD-YBOCS-A.

Other secondary clinician-rated outcomes will include the Clinical Global Impressions Scale—Severity (CGI-S) and the Clinical Global Impressions Scale—Improvement (CGI-I), compared with baseline [41], as well as the Children’s Global Assessment Scale (CGAS) to assess global functioning of the young person [42]. All assessors will be trained in the use of the CGI-S, CGI-I, and CGAS and will rate them in addition to the BDD-YBOCS-A.

Secondary child/adolescent- and parent/caregiver-reported outcomes will include the self-reported Appearance Anxiety Inventory (AAI) to assess typical BDD cognitions and behaviors [43, 44]; the Short Mood and Feelings Questionnaire—child version (SMFQ-C) and parent version (SMFQ-P) to evaluate depressive symptoms [45], including an additional suicide item (only for the child/adolescent); the self-reported Generalized Anxiety Disorder—7-item scale (GAD-7) to assess anxiety [46]; the Deliberate Self-Harm Inventory—youth version (DSHI-Y-7) to assess the presence and frequency of non-suicidal self-injuries [47]; the self-reported CRAFFT (acronym for the key words Car, Relax, Alone, Forget, Friends, and Trouble) to identify substance use and substance use disorder [48, 49]; the Work and Social Adjustment Scale—youth version (WSAS-Y) and parent version (WSAS-P) to assess functional impairment [50, 51]; the Working Alliance Inventory—child version (WAI-C) and parent version (WAI-P) to measure perceived working alliance with the therapist [52]; the Client Satisfaction Questionnaire (CSQ-8) to assess treatment satisfaction in both the child/adolescent and their parents/caregivers [53]; the Treatment Credibility and Expectancy Scale (TCES) to measure treatment credibility or expectancy of treatment outcome [54]; the Patient Exposure Adherence Scale (PEAS) or Patient Relaxation Adherence Scale (PRAS)—according to group allocation—to measure patient adherence to either of the interventions [55]; and two items to assess treatment preference in both the child/adolescent and the parent/caregiver. Additionally, for the health economic evaluation, the child/adolescent will complete the self-reported Child Health Utility 9D (CHU9D), assessing quality of life [56], and the parent/caregiver will complete the Treatment Inventory of Costs in Patients with Psychiatric Disorders (TIC-P), assessing healthcare and societal resource use [57].

#### Additional measures

Additional measures will include demographic data, body areas of BDD-related concern, desire and/or undertaking of cosmetic procedures, school attendance, concurrent interventions, number of completed treatment modules, BASS platform usage data, and therapist time, including written messages in the platform and telephone calls.

### Safety procedures

A questionnaire will be administered to systematically assess adverse events throughout the trial. The questionnaire was developed by the research team and includes a checklist of expected adverse events based on previous trials as well as a free text box where other, not listed adverse events can be registered. Additionally, high scores on the SMFQ (depressive symptoms), with the additional suicide item, and the DSHI-Y-7 (self-harm) might also be indicators of adverse events. Scores ≥13 points on the SMFQ-C or SMFQ-P, or scores of 2 (“*I have had thoughts about death and of taking my life, but would never do it*”) or 3 (“*I have had thoughts about death and of taking my life*”) points on the suicide item on the SMFQ-C, will automatically raise a flag in the BASS system that will directly notify members of the research team to follow this up (via telephone) with the participant and their parents/caregivers. This will be recorded as an adverse event if the score is greater than their baseline score. The research team can also be notified about adverse events through direct (text or telephone) communication with the participant.

All adverse events will be documented at each of the sites by the corresponding local study coordinator in a specific log (including date, recorded clinical symptoms, and a brief description of the event), which in turn will be shared with the external monitor, the KTA. All adverse events will be summarized by number (frequencies and percentages), nature, severity, and whether they are expected or unexpected. The event will be classified as expected if it was listed as such in the study protocol (e.g., increased severity of BDD symptoms, lower mood, increased risk of self-harm, suicidal ideation, and/or suicide attempt; see Supplementary File 1 for the full list). If the event is not listed, then it will be classified as unexpected. If there are any serious adverse events (i.e., those resulting in death, life-threatening, requiring hospitalization, resulting in disability or incapacity, or considered medically significant by the principal investigator), the study coordinator and the principal investigator will judge whether these are related to the treatments provided. Events will be considered as potentially treatment-related up to the 6-month follow-up.

Appropriate action will be taken in the case of a serious adverse event, making sure the participant gets in contact with suitable health care services. If a serious adverse event occurs, the principal investigator will immediately notify the sponsor and the monitor; then they will work together to identify the extent of the serious adverse event and determine whether and what urgent safety measures are required.

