### Participants

#### Eligibility criteria

The inclusion criteria for participation are (1) a primary diagnosis of BDD, based on the 5th edition of the Diagnostic and Statistical Manual of Mental Disorders (DSM-5) [32]; (2) a total BDD symptom severity score ≥24 on the Yale-Brown Obsessive-Compulsive Scale Modified for Body Dysmorphic Disorder, Adolescent version (BDD-YBOCS-A); (3) age between 12 and 17 years; (4) a minimum of one available parent/caregiver able to co-participate and support the adolescent throughout the treatment; and (5) regular access to a computer connected to the Internet and a mobile phone to receive text messages.

The exclusion criteria are (1) previous CBT for BDD for a minimum of five sessions with a qualified therapist within the 12 months prior to the inclusion assessment; (2) simultaneous psychological treatment for BDD or for any psychiatric comorbidity; (3) initiation, change of dosage, or cessation of any selective serotonin reuptake inhibitors (SSRIs) or antipsychotic drugs within the 6 weeks prior to the inclusion assessment; (4) a diagnosis of organic brain disorder, intellectual disability, psychosis, bipolar disorder, eating disorder, severe depression, or alcohol/substance dependence; (5) immediate risk to self or others requiring urgent medical attention or inpatient care, such as suicidality, or repeated self-injurious behaviors; (6) a documented suicide attempt in the last 12 months; (7) adolescent and parent/caregiver not able to read and communicate in Swedish; or (8) having a close relationship to an already included participant (e.g., sibling, cousin), to avoid being randomized into two different arms, with the risk of information “leaking” between the groups.

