### Interventions

#### Treatment format and therapist support

Both treatments are delivered over the Internet using BASS, a digital platform provided by the eHealth Core Facility at Karolinska Institutet that is also used as a data collection tool and database for storing the data. Both interventions are therapist-guided and consist of two separate sets of modules, one for the child/adolescent and one for the parent/caregiver, each with separate logins.

Table 1 contains an overview of the content of the interventions. Each intervention consists of 12 modules delivered over a maximum period of 14 weeks. During this time, participants (both the child/adolescent and the parent/caregiver) have regular contact with a therapist in the platform. The therapist will provide brief asynchronous support during the treatment, which includes feedback, answering questions, and sending reminders to complete the next module, if required. Communication during the treatment is possible via text messages in the online platform (resembling e-mail). The therapist usually logs in daily (on workdays, at least every 48 h). There are no specified limits to the therapist’s time. Telephone calls are possible if the participant or the therapist feel that they are needed. The participants are welcome to contact their therapist at any time, who will reply during office hours.

**Table 1 Tab1:** Overview of the treatment modules for both child/adolescent and parents/caregivers in each condition

Module	Internet-delivered cognitive-behavior therapy arm	Internet-delivered relaxation training arm
1	Introduction and information about body dysmorphic disorder	Introduction and information about body dysmorphic disorder
2	Learning more about body dysmorphic disorder and set up treatment goals	Learning more about body dysmorphic disorder
3	What is exposure therapy?	What is anxiety?
4	Starting exposure practice	Starting relaxation practice: deep breathing
5	Focus on response prevention	Relaxation practice: arms, legs, and back
6	How body dysmorphic disorder affects family and school	Relaxation practice: head, jaw, neck, stomach, and chest
7	Body dysmorphic disorder thoughts and attention training	Relaxation practice: whole body
8	Full response prevention	Imagery (cognitive relaxation)
9	Exposure with response prevention practice	Relaxation with and without audio file in different positions
10	Exposure with response prevention practice	Repeating previously practiced relaxation exercises

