### Ethics

The Swedish Ethical Review Authority approved the study (original application reference number 2023–02193-01 and amendment reference number 2024–02036-02). The original ethical approval document and an automatically generated English translation of this document are available in Supplementary Files 3 and 4. Verbal information about the study and written informed consent forms are provided to the child/adolescent and all legal guardians prior to baseline assessment. All participant families are volunteers competent to provide informed consent. Participants may withdraw from the trial at any time. The informed consent form includes a provision informing participants that de-identified data collected during the trial may be used in future research projects and may be shared with other researchers in accordance with applicable ethical approvals, legal requirements, and data protection regulations. No biological specimens will be collected.

The interventions pose a small risk to participants. Both interventions (ICBT and IRT) differ from their respective face-to-face versions only in the format and mode of delivery but still contain the same evidence-based components. While there is some preliminary evidence to suggest that ICBT may be efficacious for individuals with BDD [16, 26, 28, 29], at present, there is no evidence that it will be superior to IRT in reducing BDD symptom severity. Thus, the trial fulfills the principle of equipoise. Nonetheless, our hypothesis is that ICBT may indeed be superior to IRT. For that reason, all individuals randomized to the active comparator (IRT) will be offered crossover after the controlled period ends at the 1-month follow-up.

Patient safety is of high priority in this study. Participants complete measures of depression and suicidality weekly, allowing for these symptoms to be monitored throughout the intervention. A thorough diagnostic and mental health status examination before enrollment of participants will prevent patients with more immediate needs or risks from being included in the study. Children and adolescents who have recently (during the previous year) attempted suicide will be excluded to reduce the risk of suicide attempts and increase patient safety during the trial. These patients will be referred to other services or offered alternative treatment at the clinic, as appropriate.

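### SMFQ scores of 13 or more count as adverse events after any rise over one baseline score, so ordinary fluctuation inflates the adverse-event percentage and dilutes a difference between arms

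*Protocol article*

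**What the plan says.** The relevant text is in the Protocol article.

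- **Trigger (Safety procedures).** "Scores ≥13 points on the SMFQ-C or SMFQ-P", or a 2 or 3 on the added suicide item, sets off an automatic flag and a telephone follow-up.
- **Recording (same section).** "This will be recorded as an adverse event if the score is greater than their baseline score". The article attaches no minimum increase, no repeat measurement and no confirmation criterion. It does not say how repeated flags in one participant are counted.
- **Frequency (Ethics).** "Participants complete measures of depression and suicidality weekly, allowing for these symptoms to be monitored throughout the intervention". The sentence names no instrument and does not say whether the parent form is weekly. The measurement schedule (Table 2) is not visible in the text at hand.
- **Duration (Treatment format and therapist support).** "12 modules delivered over a maximum period of 14 weeks".
- **Other sources of events (Safety procedures).** "A questionnaire will be administered to systematically assess adverse events throughout the trial". Events can also be reported by text message or telephone.
- **Summary (same section).** "All adverse events will be summarized by number (frequencies and percentages), nature, severity, and whether they are expected or unexpected". Source of the event is not among the listed breakdowns.
- **Population (Eligibility criteria).** The diagnostic exclusions include "eating disorder, severe depression, or alcohol/substance dependence", so adolescents with mild or moderate depressive symptoms can enter.

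**The concern.** One baseline score, itself measured with error, is the reference for about a dozen later scores, and a single point above it is enough once the score reaches 13. A participant who goes from 12 to 13 in one week, or from 15 to 16, has an adverse event. One who goes from 3 to 12 and stays there has none by this route. The rule therefore responds strongly to how close a participant starts to 13 and to how many questionnaires are completed, and only in part to worsening.

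These events enter the same frequencies and percentages as events that a participant, parent or therapist noticed and reported. The Discussion names safety as one of the conditions for introducing ICBT into regular care, and readers will compare the two adverse-event percentages whether or not a test is planned. If both carry a large share of noise, a real excess of mood worsening in one arm is harder to see. Unequal questionnaire completion between arms could also shift the percentages.

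**Working it through.** **What the plan gives.** There is no expected adverse-event rate and no SMFQ SD or reliability, so no stated figure on this point can be reproduced. The only planned number used below is the group size: 128 × 1.2 = 153.6, rounded to 154, or 77 per arm, as in Power analysis.

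**Step 1: simple reference points.** With a constant true level and exchangeable continuous scores, the chance that at least one of 12 later scores exceeds baseline is 1 − 1/13 = 12/13 = 92%. This is not the event probability, because it ignores the floor of 13 and ties between whole-number scores. A second view: if the weekly chance of an event is p and weeks are independent, the chance of at least one in 12 is 1 − (1 − p)^12. For p = 0.10 this is 1 − 0.9^12 = 72%; for p = 0.20 it is 1 − 0.8^12 = 93%.

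**Step 2: simulation with the floor and ties.** An event is a score of at least 13 that is above baseline. Assumptions not in the documents: whole-number scores 0 to 26, population mean 12, between-person SD 5.5, one baseline and 12 weekly scores, and autoregressive week-to-week error. The table shows the share with at least one event among participants with baseline 10-16. Each range runs over error correlation 0.8 to 0.

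| Within-person SD | No mean change | Mean fall of 3 | Mean fall of 6 |
|---|---|---|---|
| 1 | 56-70% | 20-39% | 7-25% |
| 2 | 72-83% | 48-65% | 30-50% |
| 3 | 78-88% | 62-77% | 47-65% |
| 4 | 82-91% | 70-83% | 58-74% |

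With no mean change and error correlation 0.5, such a participant has on average 4.2 qualifying weeks at SD 2 and 4.6 at SD 3. If the parent form is also weekly (assumed correlation 0.4 with the child form), the share for SD 1 to 3 becomes 81-94% with no change and 48-86% with a fall of 3.

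**Step 3: what this does to the arm comparison.** Whole sample, 77 per arm, error correlation 0.5, one arm truly worse by a constant amount. Power is for a two-sided comparison of the proportions with at least one event. The last two columns also require a rise of at least 5 points, for illustration only.

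| SD, mean course | True difference | Stated rule | Power | Rise of at least 5 | Power |
|---|---|---|---|---|---|
| 3, no change | 2 | 66% vs 80% | 0.54 | 37% vs 59% | 0.78 |
| 3, no change | 3 | 66% vs 85% | 0.82 | 37% vs 68% | 0.98 |
| 2, no change | 2 | 57% vs 76% | 0.69 | 17% vs 44% | 0.96 |
| 3, fall of 3 | 2 | 52% vs 71% | 0.68 | 22% vs 43% | 0.79 |
| 2, fall of 3 | 2 | 41% vs 65% | 0.87 | 6% vs 24% | 0.88 |

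The rule loses information, most clearly when mood does not improve on average and hardly at all in the last row. Event counts still differ: at SD 3 with no change and a 2-point difference, 3.1 against 5.1 per participant.

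**Step 4: would a stricter summary cut the noise?** Baseline 10-16, no change, error correlation 0.5: at SD 2 the share falls from 80% under the stated rule to 60% if two consecutive weeks are needed, and to 22% if a rise of at least 5 is needed. At SD 3 the figures are 85%, 66% and 45%. Persistence alone helps only moderately. Requiring both cannot give more than the smaller of the two figures.

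**The case against.** A reader might infer that the safety result cannot separate the arms. The documents do not support that. The same rule applies to both randomized arms, so noise dilutes a difference, and Step 3 shows useful power remaining in many settings. A reader might also infer that most participants with moderate depressive symptoms will have an event. That rests on an SMFQ variability and course that the documents do not give. All participants receive a therapist-guided treatment, so some improvement is plausible, and with low variability and a 6-point fall the share drops to 7%.

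Much is already planned. Events are also summarized by nature, severity and expectedness, and lower mood is a listed expected event. Serious adverse events are defined and judged separately. The SMFQ is a secondary outcome analysed in the primary outcome's modelling framework, which compares mood between arms without using this rule. Sensitive capture is a defensible choice in adolescents at elevated risk of suicidality. The weekly use of the SMFQ is inferred, and the full protocol may say more about confirmation or repeated flags. Safety is not among the stated aims, and no between-arm test of adverse events is described.

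All of this stands and limits the point. It does not remove it. The recording sentence is a stated definition without a minimum rise. Tabulating by nature does not separate a one-point rise from a reported deterioration when both are lower mood. The model of mean SMFQ scores does not correct the adverse-event percentage that readers will see.

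**Conclusion.** The point holds in a limited form. As written, the rule turns any excess over one baseline score into an adverse event once the SMFQ total reaches 13, and these events are pooled with those from other sources. If the SMFQ is scored weekly, this inflates the adverse-event percentage and dilutes, without removing, a difference between arms.

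The size depends on assumptions: at a within-person SD of 2 to 3 and error correlation of 0 to 0.8, at least one event in about 72-88% of participants with baseline 10-16 when nothing changes, about 48-77% with a mean fall of 3 and 30-65% with a mean fall of 6. Serious adverse events and the planned SMFQ model are unaffected. The weakness is in how the safety summary can be read; it gives no reason to alter the monitoring itself.

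**What to change.** Leave the flag, the telephone follow-up and the recording of events, including rises on the suicide item, exactly as they are. Change only the safety summary, in the article's safety section or the analysis plan:

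1. Tabulate by arm the events triggered only by an SMFQ total score, separately from events reported by checklist or direct contact, confirmed at the follow-up call, or triggered by the suicide item. State how repeated flags in one participant are counted.
2. Add by arm the proportion of participants with an SMFQ rise above a size fixed before unblinding and sustained on two consecutive scores. Defining this without the floor of 13 would also show large rises that stay below it.

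The sustained-rise summary can be derived from stored scores for everyone, including the 100 participants recruited by 21 August 2026. There is time: the analysis plan is to be finalized before the last participant reaches the primary endpoint, expected in March 2028.

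The cost is one more table and a derived variable. The split by source also needs the event log to show how each event came to notice; if it does not for earlier events, they have to be classified from their descriptions.
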